#### Dropout rates

We will calculate the number of participants who complete the 6-month participation period as a proportion of the total number of participants who were randomised into the study.

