##### Retrospective versus momentary assessments

Participants will be asked to complete monthly assessments at irregular intervals for 6 months. Whenever an assessment is due (as per the sampling protocol), a notification will be displayed on a participant’s handset. There will be two types of notifications: one for the *Check Back* feature and one for the *Check In* feature of BrightSelf. The visual appearance of the notifications will depend on the operating system and on the model of the participant’s handset. The text of the notifications, however, will remain constant across participants for each type of notification.

Participants will be able to respond (and thus complete the corresponding assessments) or to dismiss the notifications. In addition, participants will be able to leave notifications unanswered. If participants do not complete an assessment in response to a notification, they will not receive reminders or follow-up notifications. In these instances, the non-response will be recorded in our database and will be coded as such for the purposes of our data analysis.

Outside assessment periods, participants will be able to use BrightSelf in any way they find convenient and there will be no restrictions on the number of assessments they can complete on a single day. However, we will be able to distinguish between assessments completed in response to a notification and those completed spontaneously. At baseline, participants will be randomly allocated to one of two types of assessment strategies:

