##### Retrospective plus momentary assessments

In this experimental manipulation, participants will be asked to complete a combination of retrospective assessments and momentary assessments. A retrospective assessment will be defined as a single administration of the EPDS. A momentary assessment will be defined as the five momentary questions plus the two contextual questions.

Participants will be required to complete assessments for a total of 6 months, and each assessment period will consist of six consecutive days. The 6-month participation period will be calculated from the day on which the app is activated (ie, when participants enter their activation code and activate their account), and it will be divided into six intervals. All participants will receive the first notification 2 days after activating BrightSelf (ie, first assessment), while the use of the app is fresh within their minds and to give an idea of what to expect during the study. Subsequent assessment periods will be a random selection of six consecutive days within the 21–35 days following the end of the previous assessment period (in order to avoid 12 days of continuous assessments).

The assessment period will be structured as follows:Day 1: one retrospective assessment at any random time between 17:00 and 21:00Days 2–5: three momentary assessments per day, displayed at random times within each of the following intervals: 09:00–12:00, 13:00–16:00 and 17:00–20:00Day 6: one retrospective assessment at any random time between 17:00 and 21:00.

At the end of the 6-month period, participants will be sent a link via SMS or by e-mail to complete the non-validated, poststudy acceptance survey.

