### Outcomes

#### Adherence to sampling protocols

We will calculate the number of participants who complete 100% of the expected assessments (as per the study protocol) as a proportion of the total number of participants who were randomised into the study. We will subdivide this outcome by using the total number of participants who complete the 6-month participation period as the denominator.

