### Sample size calculations

We have chosen to relate the proposed sample size to the 95% CI for the adherence rate, as recommended by the Research Design Service in London. Therefore, we would need 96 participants in each arm with a 95% confidence level and a CI of 10. This translates into a total sample of 192 (ie, 96 participants in each experimental group). For this reason, we will aim to recruit at least 250 participants to account for dropouts and potential miscarriages.

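### The outcome headed Dropout rates is defined as the share who complete, which is the retention rate, and completing the period is itself not defined

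*Protocol article*

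**What the plan says.** The Dropout rates section consists of one definition: "the number of participants who complete the 6-month participation period as a proportion of the total number of participants who were randomised". The outcome is called dropout in the Abstract (Methods and analysis), in the Introduction, where it stands beside adherence as a measure of patient acceptance, and under Inferential statistics, where the two arms are compared on it.

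The group of completers is used a second time. Under Adherence to sampling protocols, the proportion with all expected assessments is also to be calculated "using the total number of participants who complete the 6-month participation period as the denominator".

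On what completion means, both arm descriptions fix the start of the clock ("The 6-month participation period will be calculated from the day on which the app is activated") and say that assessments are required over the six months. Neither says what a woman must have done to count as a completer.

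The section Retrospective versus momentary assessments says that "participants will be able to leave notifications unanswered" and that, after a missed assessment, "they will not receive reminders or follow-up notifications". It also says that "the non-response will be recorded in our database and will be coded as such for the purposes of our data analysis".

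The sample size section raises the target from 192 to at least 250 "to account for dropouts and potential miscarriages", without giving a dropout rate.

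**The concern.** The formula and its name point in opposite directions. Completers over randomised rises when more women stay, and a dropout rate rises when more women leave. An analyst who follows the definition exactly will publish a retention figure as dropout, and the arm that retains better will appear to lose more women.

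This matters because dropout is one of the two acceptance measures named in the Introduction and one of three outcomes compared between arms. It bears directly on whether the heavier sampling schedule drives women away. The Conclusion says the findings will inform a larger trial, so a reversed figure could be carried into its planning.

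The second, smaller issue is that completion has no operational meaning in the article. In a study run through a phone app, with unanswered notifications allowed and no reminders, a woman can stop responding without telling anyone. Whether she is a completer or a dropout depends on a rule the article does not give.

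**Working it through.** **1. The plan's own figures.** The sample size section gives 96 per arm, a 95% confidence level and a CI of 10. Reading the last as ±10 percentage points, and assuming a proportion of 0.5:

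n = 1.96² × 0.5 × 0.5 / 0.10² = 96.04, which reproduces 96 per arm and 2 × 96 = 192 in total.

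The target of 250 then implies a loss of 1 − 192/250 = 0.232. The article does not state this rate; it only follows from the two totals.

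**2. The definition applied as written.** Suppose 192 of 250 women complete.

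- Rule under Dropout rates: 192/250 = 76.8%
- Dropout: 1 − 192/250 = 23.2%

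**3. Effect on the arm comparison.** Take 125 per arm and assumed completion of 70% and 80%.

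- As written, the dropout rates are 70% and 80%, so the second arm looks worse by 10 points.
- Actual dropout is 30% and 20%, so the second arm is better by 10 points.

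If X is 1 for a completer and 0 otherwise, the mean of 1 − X is 1 minus the mean of X, and the variance is the same. A two-sided test therefore gives the same p-value. The power calculation agrees: 0.446 for 0.70 against 0.80, and 0.446 for 0.30 against 0.20. The sample size rests on adherence and is not touched.

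**4. How much the missing definition of completion could matter.** Assume 250 randomised and 20 formal withdrawals or miscarriages (neither the 20 nor the numbers below come from the article). Assume also that anyone who reaches the end date without withdrawing counts as a completer.

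| Silent stoppers | Rule as written | Its complement | Dropout with silent stoppers counted |
|---|---|---|---|
| 0 | 92.0% | 8.0% | 8.0% |
| 25 | 92.0% | 8.0% | 18.0% |
| 50 | 92.0% | 8.0% | 28.0% |
| 75 | 92.0% | 8.0% | 38.0% |
| 100 | 92.0% | 8.0% | 48.0% |

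The second adherence denominator moves too. With 50 silent stoppers it is 250 − 20 = 230 on the calendar reading and 230 − 50 = 180 if they are excluded.

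**5. Check on a possible log-based rule.** One candidate is to call a woman active if she answers any scheduled EPDS in the last assessment period. The combined arm has two EPDS prompts per period (days 1 and 6) and the retrospective arm has one. With an assumed 60% response to each prompt, independent and equal in both arms:

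- Combined arm: 1 − (1 − 0.6)² = 84%
- Retrospective arm: 60%

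That rule would create a 24-point difference where none exists.

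**The case against.** The best defence of the definition is that it does little harm. Numerator and denominator are both stated, so a careful reader can subtract from 1, and neither the test nor the sample size changes. That is correct, and it limits the damage to the reported value and its direction. It does not make the definition right. No reading of the section yields a dropout rate, and this is a wrong statement in the article rather than detail left to a fuller document.

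A reader might go further and infer that completion is purely calendar time, so that the outcome is blind to women who silently stop. The article does not support that as a fact. The arm descriptions say when the six months begin, not who has completed them, and they also require assessments throughout. Using completers as a separate denominator for full adherence shows that completing the period differs from completing every assessment. That makes the calendar reading plausible but does not establish it. An operational rule may stand in the full protocol or analysis plan.

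Nor would silent stopping be invisible to the study. Each non-response is recorded and coded. Adherence over all randomised, timeliness over all expected assessments, and the usage logs would all respond to it. The compensation is partial: adherence requires 100%, so one missed prompt looks the same as abandonment, and timeliness counts assessments rather than women.

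A reader might also infer that pregnancy loss is wrongly merged with disengagement. The sample size section names the two separately, and tabulating reasons for leaving is detail an article commonly omits. It is not an error here.

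**Conclusion.** The inversion is certain from the text. The outcome called dropout is defined as retention, and nothing elsewhere corrects it. Followed as written, it would report 76.8% instead of 23.2% if 192 of 250 complete, and it reverses the direction of the arm difference. It does not alter the p-value or the sample size. The 192 and 250 are the plan's own totals, used as an example and not as a forecast. The definition should be corrected before any result is reported.

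The undefined meaning of completion is a secondary point. It is a risk, not a demonstrated fault. On the calendar reading, and with the assumed numbers above, the dropout figure could stay at 8% while the share of women who had stopped or left ranged from 8% to 48%. If the full protocol contains a rule based on activity, this part falls away.

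**What to change.** - Define dropout rate = 1 − (completers / randomised), or keep the present formula and rename the outcome retention. Use the chosen term consistently in the Abstract, the Introduction, the Dropout rates section and the Inferential statistics section.
- State in one sentence what makes a participant a completer, and use the same rule for the second adherence denominator.
- If that rule is taken from the app logs, give both arms the same opportunity to be counted. One option is time to the last answered Day-1 EPDS, which sets one prompt per period against one prompt per period. Do not use any EPDS in the final period, for the reason shown in step 5. Count in assessment periods rather than days: each gap runs from the end of the previous period, and a period lasts six days in one arm and one day in the other.

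The cost is a change of wording. Responses and non-responses are already recorded, so no new data are needed. The downside is that reported retention may look less favourable once women who have silently stopped are classified.

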#### Usage patterns

We will assess participants’ usage pattern of BrightSelf by analysing log data (additional variables capturing app usage). These will include the number of additional voluntary self-reports, time spent using the app, number of interactions with other sections of the app, time taken to complete the self-assessments and other ancillary usage data.

#### Acceptance

We will calculate participants’ ratings and responses to the poststudy acceptance survey. In addition, we will conduct thematic analysis of participants’ answers to the open-ended questions of this survey using Atlas.ti 8.^32^

#### Timeliness of data completion

We will calculate the number of assessments that were completed in response to a notification as a proportion of the total number of expected assessments. We will subdivide this outcome by using the total number of completed assessments as the denominator. We will consider that an assessment has been completed in response to a notification if it takes place within the interval corresponding to that notification (ie, before the next notification is delivered). This broad interval may raise concerns regarding the ecological validity of the report, which we will explore in our statistical analysis.

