##### Retrospective assessments

In this experimental manipulation, participants will be asked to complete retrospective assessments only. A retrospective assessment will be defined as a single administration of the EPDS.

Participants will be required to complete assessments for a total of 6 months, and each assessment period will consist of 1 day. The 6-month participation period will be calculated from the day on which the app is activated (ie, when participants enter their activation code and activate their account), and it will be divided into six intervals. Again, all participants will receive the first notification 2 days after activating BrightSelf (ie, first assessment). Subsequent assessments will take place on a random day within the 21–35 days following the end of the previous assessment period (in order to avoid two consecutive EPDS assessments).

On each assessment day, participants will receive a notification to complete the EPDS at a random time between 17:00 and 21:00.

At the end of the 6-month period, participants will be sent a link via SMS or by e-mail to complete the non-validated, poststudy acceptance survey (see figure 3 for an illustration of both sampling protocols).

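### Timeliness is judged by a window that runs to the next notification: 21–35 days in the retrospective arm, 1–28 hours for 13 of 14 prompts in the combined arm, so the comparison favours the retrospective arm

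*Protocol article*

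**What the plan says.** Under Outcomes, Timeliness of data completion, the measure is "the number of assessments that were completed in response to a notification as a proportion of the total number of expected assessments". A second version changes the denominator: "We will subdivide this outcome by using the total number of completed assessments as the denominator". An assessment qualifies "if it takes place within the interval corresponding to that notification (ie, before the next notification is delivered"). The section adds one caveat: "This broad interval may raise concerns regarding the ecological validity of the report, which we will explore in our statistical analysis".

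The two schedules differ. In the retrospective arm "each assessment period will consist of 1 day", with one EPDS prompt between 17:00 and 21:00, and then "Subsequent assessments will take place on a random day within the 21–35 days following the end of the previous assessment period". In the combined arm (section Retrospective plus momentary assessments) each period has 14 prompts over six days: an EPDS on Day 1 (17:00–21:00), three momentary prompts a day on Days 2–5 (09:00–12:00, 13:00–16:00, 17:00–20:00), and an EPDS on Day 6 (17:00–21:00). The next period then follows within 21–35 days.

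The section Retrospective versus momentary assessments allows free use of the app outside assessment periods ("there will be no restrictions on the number of assessments they can complete on a single day") and states that "we will be able to distinguish between assessments completed in response to a notification and those completed spontaneously".

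Inferential statistics names timeliness as one of three outcomes compared between arms, by t-test or a non-parametric equivalent. It plans a look at notification-to-report delays for momentary assessments only.

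**The concern.** A timeliness measure should give the same score to the same behaviour. Here the time allowed is fixed by how soon the next prompt happens to arrive, and that is the feature on which the arms differ by design. A retrospective-arm participant who completes the EPDS three weeks after her prompt is timely. A combined-arm participant who completes the Day 1 EPDS the following afternoon is not. The EPDS asks about the past 7 days, so the three-week-late report does not even describe the week that was prompted.

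The rule also conflicts with the promised separation of prompted from spontaneous reports. In the retrospective arm, a voluntary EPDS made weeks after an unanswered prompt falls inside that prompt's interval and is scored as a response to it.

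At stake is the reading of one of the three between-arm comparisons. A difference could be reported as an effect of assessment burden when the definition alone produced it.

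**Working it through.** The protocol gives no figure for timeliness to reproduce. Its one computed figure, 96 per arm, is reproduced by 1.96² × 0.25 / 0.10² = 96.04, but it concerns adherence and does not bear on this point.

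**Step 1. Windows from the schedules** (time from one notification to the next of any type)

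| Prompt | Number per period | Window |
|---|---|---|
| Retrospective arm, EPDS | 1 | 21–35 days, midpoint 28 days = 672 h |
| Combined, Day 1 EPDS | 1 | 21:00 to 09:00 = 12 h, up to 17:00 to 12:00 = 19 h; midpoint 15.5 h |
| Combined, 1st and 2nd momentary, Days 2–5 | 8 | 12:00 to 13:00 = 1 h, up to 09:00 to 16:00 = 7 h |
| Combined, 3rd momentary, Days 2–4 | 3 | 20:00 to 09:00 = 13 h, up to 17:00 to 12:00 = 19 h |
| Combined, 3rd momentary, Day 5 | 1 | 20:00 to next-day 17:00 = 21 h, up to 17:00 to next-day 21:00 = 28 h |
| Combined, Day 6 EPDS | 1 | about 21–30 days if the whole next period must fit within days 21–35; up to 35 days otherwise |

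So 1 + 8 + 3 + 1 = 13 of 14 combined-arm windows (93%) last 1–28 h, and 8 of 14 (57%) last at most 7 h. Simulating the schedule (100,000 draws) gives a median combined-arm window of 5.5 h, against 28 days in the retrospective arm. In both arms the last notification has no successor, so its window has no stated end.

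**Step 2. Same behaviour in both arms, Day 1 EPDS against retrospective EPDS**

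Assumption: delay is lognormal with median m and log-SD 1.5, everyone eventually responds, and each report is credited only to its own prompt. Then P(timely) = Φ(ln(window/m)/1.5).

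| Assumed median delay | Day 1 EPDS (15.5 h) | Retrospective EPDS (672 h) | Difference |
|---|---|---|---|
| 1 h | 96.6% | 100.0% | 3 points |
| 3 h | 86.3% | 100.0% | 14 points |
| 6 h | 73.7% | 99.9% | 26 points |
| 12 h | 56.8% | 99.6% | 43 points |
| 24 h | 38.5% | 98.7% | 60 points |

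For m = 12 h: ln(15.5/12)/1.5 = 0.171, Φ = 0.568; ln(672/12)/1.5 = 2.684, Φ = 0.996.

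**Step 3. Other readings**

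- *Day 1 and Day 6 EPDS pooled.* With a Day 6 window of about 672 h and m = 12 h, the combined arm scores (56.8 + 99.6)/2 = 78.2%. The gap is 99.6 − 78.2 = about 21 points, half of that in Step 2.
- *Next notification of the same type.* The Day 1 EPDS window becomes about 5 days = 120 h. At m = 12 h, Φ(ln(120/12)/1.5) = 93.8% against 99.6%, about 6 points. Eleven of the 14 windows are still 1–19 h.
- *All 14 prompts, exponential delay* (a different assumed shape). Combined against retrospective: 95% v 100% at a 1 h median, 76% v 100% at 3 h, 59% v 100% at 6 h, 41% v 100% at 12 h, 28% v 100% at 24 h.

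**Step 4. The completed-assessments denominator**

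In the retrospective arm the EPDS is the only assessment, and the intervals between notifications leave no gaps. Any EPDS completed between the first and last notifications therefore lies in some prompt's interval. Numerator and denominator then coincide, and the ratio goes towards 100% whatever participants do.

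**The case against.** The authors did not overlook the width of the interval. They flag it, and they plan to examine the distribution of delays. This is a feasibility study sized on adherence, and time-stamped logs would allow timeliness to be re-derived later. These points lower the cost of repair but do not answer the concern. The caveat is about ecological validity, and the delay analysis covers momentary reports, which the retrospective arm does not have. Nothing in the article addresses unequal windows in a between-arm test.

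Four stronger readings are tempting and are not supported:

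- *Every combined-arm window is a matter of hours.* The Day 6 EPDS also has about three weeks or more, so half of that arm's EPDS prompts have windows close to the retrospective arm's.
- *The artefact is 43 points.* That figure needs a 12 h median delay, the Day 1 EPDS alone and the any-type reading. The documents give no delays. The calculation also assumes that everyone eventually responds. Prompts can be dismissed or ignored without a reminder, and permanent non-response shrinks the gap in proportion.
- *Practically every report in both arms counts as a response.* This cannot stand together with the artefact in Step 2, which needs a late Day 1 EPDS not to count. If a report were credited to whatever interval it fell in, regardless of type, the gap in Step 2 would disappear. The rule ties an interval to its own notification, so the push towards 100% is secure mainly for the retrospective arm.
- *The numerator can exceed the expected number.* That follows only if the stated separation of spontaneous reports, and the separate count of voluntary self-reports under Usage patterns, are ignored. The wording needs reconciling, but overflow is not the evident intent.

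**Conclusion.** The concern holds in this form: the response window is set by each arm's prompting schedule, and under equal behaviour the timeliness comparison favours the retrospective arm. The window lengths follow directly from the protocol's schedules. The direction does not depend on the assumed delays, provided each report is credited to its own prompt. The size does depend on them: from about 3 to 60 points for the Day 1 EPDS over median delays of 1 to 24 h, about half that with Day 1 and Day 6 pooled, and about 6 points at a 12 h median under the same-type reading. If participants respond within an hour or so, the distortion in the EPDS comparison is small.

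Separately, in the retrospective arm the rule counts late spontaneous EPDS reports as responses. This conflicts with the prompted/spontaneous distinction and leaves the completed-assessments version nearly uninformative there. Applied as written, the rule biases the planned comparison, so it should be changed before the arms are compared on timeliness.

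**What to change.** - Define a response as the first assessment of the matching type after a notification, at most one per notification, within a fixed window that is identical in both arms and also closes the interval after the last notification.
- For the EPDS, set that window at no more than 12 h. This is the shortest gap after the combined arm's Day 1 EPDS, so the window never overlaps the next prompt.
- Make the main between-arm comparison like for like: Day 1 EPDS in the combined arm against the EPDS in the retrospective arm. Report Day 6 EPDS and momentary timeliness descriptively within the combined arm.
- Classify later reports as spontaneous, and state how that classification is derived, so that it agrees with the section Retrospective versus momentary assessments.
- Report the notification-to-report delay for the EPDS in both arms, with wider common windows as sensitivity analyses.

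Cost: outcome wording and log-data derivation only; prompting and data collection do not change. Reported timeliness will be lower than under the open window. The cut-off is a convention taken from the schedule rather than an established response time, which is why the delay distributions and wider windows should be shown beside it.

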#### Inferential statistics

We will compare the *retrospective and momentary assessment* and the *retrospective assessment* experimental groups for differences in adherence rates, dropout rates and timeliness of data completion. For this we will use a t-test or the non-parametric equivalent.

We will compare acceptance between the two experimental manipulations by assessing differences in participants’ rankings to those questions on a 7-point Likert scale of the poststudy acceptance survey. We will also conduct a thematic analysis of the open-ended questions of this survey.

In relation to the momentary assessments, we will examine the distribution of delays between the time of notification and time of report in order to assess the effect of this delay on the ecological validity of reports.

We will analyse usage patterns through regression modelling of log data. We will analyse participants’ momentary and retrospective assessments through time-based analyses or multilevel modelling.^33 34^ We will attempt to compare if the momentary assessments had any effect on the retrospective assessments by comparing the EPDS responses given on day 1 to those given on day 6.

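### The timeliness window closes at the next notification, so its length depends on the arm and the between-arm comparison favours the retrospective arm by construction

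*Protocol article*

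**What the plan says.** Under Outcomes, Timeliness of data completion, the protocol article defines the measure as the "number of assessments that were completed in response to a notification as a proportion of the total number of expected assessments". A second version follows: "We will subdivide this outcome by using the total number of completed assessments as the denominator". A completion counts as a response "if it takes place within the interval corresponding to that notification (ie, before the next notification is delivered". The same paragraph admits that the interval is broad and may affect ecological validity, and promises to explore this in the analysis.

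The two schedules are set out under Retrospective versus momentary assessments:

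- **Retrospective plus momentary arm.** Day 1 has an EPDS prompt between 17:00 and 21:00. Days 2–5 have three Check In prompts a day (09:00–12:00, 13:00–16:00, 17:00–20:00). Day 6 has a second EPDS prompt between 17:00 and 21:00. The next period is "a random selection of six consecutive days within the 21–35 days following the end of the previous assessment period".
- **Retrospective arm.** On one day per period, "participants will receive a notification to complete the EPDS at a random time between 17:00 and 21:00". Then: "Subsequent assessments will take place on a random day within the 21–35 days following the end of the previous assessment period".

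No reminders are sent in either arm. Under Inferential statistics, the arms are compared for "differences in adherence rates, dropout rates and timeliness of data completion". The only planned look at delay is narrower: "In relation to the momentary assessments, we will examine the distribution of delays between the time of notification and time of report".

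**The concern.** A timeliness measure should ask the same question of both arms. Here the time allowed is set by how soon the next prompt arrives, and that is part of the randomised assignment. The same questionnaire, prompted at the same time of evening, is scored against a deadline of hours in one arm and of weeks in the other.

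In the retrospective arm the measure is close to a plain completion rate, since an EPDS completed three weeks after its prompt still counts as a response to it. In the momentary arm most prompts must be answered the same day or by the next morning. Timeliness is one of three named randomised comparisons. A difference produced by the schedule could be reported as momentary assessment making women slower to respond.

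**Working it through.** **Plan's own figure.** The article states no window lengths. Its one computed figure is the sample size, which reproduces: n = 1.96² × 0.25 / 0.10² = 96.04, or 96 per arm. That is ±10 points precision for the adherence rate, not for timeliness, and nothing below rests on it.

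**Window lengths.** Each window is the time of the next prompt minus the time of this prompt, using the stated clock intervals.

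| Prompt | Number per period | Shortest | Longest | Mean |
|---|---|---|---|---|
| Momentary arm, Day 1 EPDS → first Day 2 prompt | 1 | 21:00→09:00 = 12 h | 17:00→12:00 = 19 h | 15.5 h |
| Morning → midday, midday → evening (Days 2–5) | 8 | 1 h | 7 h | 4 h |
| Evening → next morning (Days 2–4) | 3 | 20:00→09:00 = 13 h | 17:00→12:00 = 19 h | 16 h |
| Day 5 evening → Day 6 EPDS | 1 | 20:00→17:00 = 21 h | 17:00→21:00 = 28 h | 24.5 h |
| Day 6 EPDS → next period | 1 | 21 × 24 − 4 = 500 h | 35 × 24 + 4 = 844 h | 672 h |
| Retrospective arm, EPDS → next EPDS | 1 | 500 h | 844 h | 672 h |

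The momentary arm has 1 + 8 + 3 + 1 + 1 = 14 prompts per period, and 13 have windows of 28 h or less. If all six days must fit inside the 21–35 day span, the Day 6 window is 21–30 days, which changes nothing material. The last assessment has no following prompt in either arm.

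**Direction.** Let F be the delay distribution, the same in both arms. The share scored timely is the mean of F(window). F cannot decrease as the window lengthens, and no momentary-arm window is systematically longer than the retrospective one. Equal behaviour therefore scores equal or higher in the retrospective arm.

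**Size, under assumptions.** The article gives no response delays. Assume one exponential delay with median m in both arms and every prompt eventually answered. Then the share timely = mean of 1 − 2^(−window/m). For example, for the Day 1 EPDS at m = 6 h, using the mean window, 1 − 2^(−15.5/6) = 0.83. Averaging over uniform draws within the clock intervals gives:

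| Median delay | Day 1 EPDS | Day 1 and Day 6 EPDS pooled | All 14 prompts | Retrospective arm |
|---|---|---|---|---|
| 2 h | 99.5% | 99.7% | 84% | 100% |
| 6 h | 83% | 92% | 59% | 100% |
| 12 h | 59% | 80% | 41% | 100% |
| 24 h | 36% | 68% | 27.5% | 100% |

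The pooled EPDS figure is the mean of Day 1 and Day 6: at 6 h, (83% + 100%)/2 ≈ 92%. The all-prompts figure weights each row of the first table by its number per period.

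**Other reading.** If only the next prompt of the same type closes a window, the Day 1 EPDS runs to the Day 6 EPDS: 5 × 24 ± 4 = 116–124 h. At m = 24 h the share is 1 − 2^(−120/24) = 0.969, a gap of about 3 points, and less at shorter medians. The 1–7 h Check In windows are unchanged.

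**The case against.** - **Not every EPDS is affected.** A reader might take the Day 1 figures as applying to all EPDS. They do not: the Day 6 EPDS has a window of at least 21 days, much as in the retrospective arm. Pooling the two roughly halves the EPDS gap but does not remove it.
- **The size is assumed.** A reader might infer that the bias must be large because the windows differ so much. The ratio of window lengths is not a bias. If most women answer within an hour or two, the EPDS gap is negligible. This stands; only the direction is fixed by the text.
- **Same-type reading.** The article names two notification types, so the window might close only at the next prompt of the same type. That nearly removes the EPDS gap for medians up to 24 h. The wording refers simply to the next notification, so this reading is possible but less literal.
- **The authors saw that the interval is broad.** They did, but as a question of ecological validity, and they plan a delay analysis for momentary reports only. Neither addresses the comparison between arms.
- **Two further inferences fail.** One might say the rule defeats the spacing meant to avoid two consecutive EPDS assessments. It does not, because a scoring rule cannot change when notifications are sent. One might also say EPDS promptness could not be reported. Nothing in the article rules it out: a delay analysis is already planned for momentary reports, and the same calculation could be made for the EPDS. The article simply does not plan it.

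**Conclusion.** The rule is wrong as written for a between-arm comparison. The window lengths and the direction of the bias follow from the article's own schedules and definition.

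The size is conditional on response delays. Under a common exponential delay with every prompt eventually answered, the pooled EPDS gap runs from 0.3 points at a 2 h median to 32 points at 24 h. Over all prompts it runs from 16 to about 72 points. Under the same-type reading the Day 1 EPDS gap is at most about 3 points over that range.

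This should be fixed but does not threaten the study. It is a feasibility study sized on adherence, no decision threshold is attached to timeliness, and the raw data are unaffected.

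**What to change.** In Timeliness of data completion and Inferential statistics:

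1. Base the between-arm timeliness comparison on prompted EPDS, scored with one fixed window after the notification, identical in both arms. One option is 12 h, the longest window that the next prompt never cuts short for a Day 1 EPDS, with 24 h and 72 h as sensitivity analyses. The cut-off is the sponsor's choice; what matters is that it is common to both arms and fixed in advance.
2. Report Check In timeliness descriptively within the momentary arm, since the other arm has no counterpart.
3. Extend the planned delay analysis to the EPDS, shown by arm.

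The cost is a change of wording, with no new data and no change to the app, provided notification and completion times are stored for the EPDS as the momentary delay analysis already requires for Check In. There are two downsides. The retrospective arm's timeliness figure will look less favourable. Under the 12 h window, which ends between 05:00 and 09:00, some next-morning answers count as late; the longer windows show how much that matters.
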